**Table 7.4.3. Proteinuria classification criteria (NCI-CTC AE 4.0) and recommendations for prevention and treatment**

| Criteria | Definition | Prevention and treatment |
| --- | --- | --- |
| Grade 1 | Urokinase protein (+) or 24-hour urine protein excretion <1.0 g | Continuing anlotinib administration without dose adjustment |
| Grade 2 | Urokinase protein (++) or 24-hour urine protein excretion of 1.0-3.4 g | Continuing anlotinib administration without dose adjustment; Drug intervention should be considered; Monitor 24-hour urine routine and 24-hour urine protein excretion |
| Grade 3 | 24-hour urine protein excretion >3.4 g | Suspension of anlotinib; Consultation with a nephrologist specialist; Drug intervention should be performed; Dose reduction of anlotinib after recovery of proteinuria to ≤ grade 2; If grade 3 proteinuria still occurs after 2 dose reductions, anlotinib therapy should be permanently discontinued |

1. **Bleeding**

The PT and international normalized ratio (INR) should be closely monitored during the administration of anlotinib to monitor patients for bleeding tendencies and related symptoms; the drug should be interrupted if a grade 3-4 bleeding event occurs. If [upper gastrointestinal bleeding](https://www.sciencedirect.com/science/article/pii/S0025712508000023) occurs, anlotinib must be interrupted and aggressively treated according to clinical protocols should be performed.

1. **Thrombus**

If any arterial thrombosis (e.g., cerebral ischemia, stroke, angina, myocardial infarction) occurs, drug administration should be discontinued immediately and the study should be withdrawn. If symptomatic grade IV venous thrombosis occurs, drug administration should be discontinued in patients, with withdrawal from the study.

For patients with thrombotic symptoms, symptomatic treatment, surgery, or anticoagulant drugs should be scheduled immediately.

For patients with venous thrombosis, the criteria for dose adjustment are as follows:

| **Venous thrombosis** | **Dose adjustment** |
| --- | --- |
| Grade II | Anlotinib is maintained at the original dose level and closely monitored. |
| Grade III or asymptomatic grade IV | 1. Anlotinib is discontinued. 2. Symptomatic treatment with anticoagulants (small-molecular-weight heparin) 3. Anticoagulants can be administrated for at least one week and no severe (grade III, IV) bleeding patients are found after symptomatic improvement of thrombosis, with continued administration after a reduced dose level according to the investigator’s judgment. |

1. **Reversible posterior leukoencephalopathy syndrome**

Reversible posterior leukoencephalopathy syndrome (RPLS) has not been reported in the completed clinical trials of anlotinib, but has been reported in the clinical use of marketed anti-neovascularization antibodies and small molecule inhibitors.

The clinical manifestations of RPLS are headache, altered/unclear consciousness, abnormal vision/blindness, and convulsions, which are often accompanied by hypertension. At present, the etiology of RPLS is unknown. Once suspected symptoms occur, the administration should be discontinued immediately with symptomatic treatment and strict control of blood pressure. Once confirmed by imaging, patients are withdrawn from the clinical trial.

1. **Abdominal pain**

Abdominal pain is uncommon in the treatment of lung cancer with anlotinib, and most patients have tumor-associated symptoms. Meanwhile, gastrointestinal perforation has been reported occasionally in clinical trials of anlotinib and other types of antiangiogenic drugs. For patients with abdominal pain, investigators should be aware of potential gastrointestinal perforation. Once gastrointestinal perforation occurs, the administration should be discontinued immediately, withdrawal from the trial, with symptomatic treatment.

1. **Pulmonary interstitial fibrosis**

The clinician should fully understand the patient's condition and be familiar with the drugs that may induce pulmonary toxicity. The clinical symptoms and chest X-ray or CT changes are carefully observed. Once patients have unexplained symptoms such as cough, chest tightness, suffocation, dyspnea, and hemoptysis, the causes should be identified in time, and administration should be discontinued as soon as possible after excluding other causes (such as infection and heart failure). Bronchoalveolar lavage and surgical lung biopsy are important methods for the diagnosis of interstitial lung disease. At present, there is no satisfactory treatment for pulmonary fibrosis. It is recommended to correct hypoxemia and timely use glucocorticoids referring to the guidelines for the diagnosis and treatment of idiopathic pulmonary (interstitial) fibrosis issued by the Respiratory Society of Chinese Medical Association.

**Note:** If necessary, specialist consulting supports the diagnosis and treatment.

1. Concomitant Medications
   1. **Drugs prohibited or used with caution during the study**
      1. **Medications that interfere with hepatic cytochrome P450 enzymes**

CYP3A inducers (dexamethasone, carbamazepine, rifampin, and phenobarbital), inhibitors (ketoconazole, itraconazole, erythromycin, and clarithromycin), CYP3A4 substrate (simvastatin, cyclosporine, and piperidine), other medications metabolized by CYP3A4 (benzodiazepines, dihydropyridine calcium antagonist, calcium antagonists, and HMG-CoA reductase inhibitors), CYP2C9 substrate, and CYP2C19 substrate will be used cautiously.

| P450 enzyme | Substrate |
| --- | --- |
| CYP2C9 | Diclofenac, phenytoin, diclofenac, tolbutamide, and s-warfarin |
| CYP2C19 | Diazepam, promethazine, lansoprazole, and s-mephenytoin |

- - 1. **Medications that prolong the cardiac QTc**

Medications that prolong the cardiac QT will be used cautiously due to the toxicity of anlotinib will prolong the QT interval in clinical practice, and medications including but not limited to:

- Antimicrobials (clarithromycin, azithromycin, erythromycin, roxithromycin, metronidazole, and moxifloxacin);
- Antiarrhythmic drugs (quinidine, sotalol, amiodarone, disopyramide, and procaine amide);
- Antipsychotics (risperidone, fluphenazine, haloperidol, haloperidol, thioridazine, pimozide, olanzapine, and clozapine);
- Antifungal drugs (fluconazole and ketoconazole);
- Antimalarial drugs (mefloquine and chloroquine);
- Antidepressants (amitriptyline, imipramine, clomipramine, dosulepin, and doxepin).
  - 1. **Chinese medicine preparations and immunomodulators with anti-cancer effects**

This protocol prohibits the use the Chinese medicine preparations for the treatment of lung cancer that is approved by CFDA and immunomodulators (such as thymosin, interferon, interleukin-2 zilongjinpian, and fungal polysaccharides).

- 1. **Permitted concomitant medications/treatments**

All treatments that are considered by the investigator to have no effects on study endpoints may be administered, such as unconventional therapies (e.g., herbal or acupuncture) and vitamin/mineral supplements. Bisphosphonates are allowed for subjects with bone metastases during the trial. Palliative radiation therapy in a small area (<5% bone marrow region) will be permitted for subjects with uncontrolled pain of bone metastases after systemic therapy or topical analgesia. Antiviral medication should be administered during enrollment for patients with positive hepatitis B surface antigens during the screening period. Clinical co-morbidities and the emergence of various types of AEs should be treated aggressively. Any combination medications should be recorded in the electronic case report forms (eCRFs) in strict accordance with GCP regulations [[16](#_ENREF_16)].

1. Study Procedures

All patients must read and sign an informed consent form approved by the ethics committee before the initiation of the study. All study procedures are required to be performed according to the time window procedure in the schematic flow diagram (Appendix 2, flow diagrams of anlotinib in combination with gefitinib for NSCLC). Clinical observation and examination time is independent of the duration of drugs, and related examinations (including imaging examinations) are performed at each course of treatment.

- 1. **Screening**

The following procedures must be completed within 4 weeks before study drug initiation (unless specifically indicated).

(1) Sign the informed consent form;

(2) Demographic: Age, sex, occupation, nationality, height, and weight;

(3) Smoking history: Smoking duration, number of cigarettes (light smokers ≤15 cigarettes/day; medium smokers <25 cigarettes/day; heavy smokers ≥25 cigarettes/day)

(4) Tumor diagnosis: Date of diagnosis for clinically staged, histologic classification (large cell carcinomas and adenocarcinomas), pathological regional (primary and metastatic lesions), TNM classification, and clinical staging.

(5) Gene mutation status (the test results of mutation status must be provided if the patient has been tested).

- EGFR gene mutation status;
- Other gene mutation status (if have).

(6) History of antitumor therapy:

- Tumor surgery: The date and type of previous surgery;
- History of chemotherapy/targeted/immunotherapy (including neoadjuvant and adjuvant therapy): Drug names, dose, administration cycle, onset and duration, best efficacy, and reasons for changing drugs (if due to disease progression, imaging should be recorded; if due to intolerance, AEs and grade of AEs should be recorded).
- Radiotherapy history: radiotherapy time and radiotherapy dose.

(7) The date of the tumor progression or recurrence after the last treatment.

(8) Comorbidities: Such as diabetes, hypertension, or chronic obstructive pulmonary disease.

(9) BP monitoring: BP is measured by the investigator during the screening period; Coffee and tobacco intake are prohibited within 30 minutes before each BP is measured and the measurement is taken in the sitting position with the arm at heart level after at least 10 minutes of quiet sitting, and each BP measurement is taken on the same side.

(10) Imaging examination (CT or MRI): Enhanced CT of the chest, abdomen and enhanced MRI of cranial. For subjects with bone metastases, a whole-body bone scan should be performed; Patients with stable brain metastases should be confirmed without intracranial hemorrhage within 21 days before randomization (written informed consent must be obtained before performing any imagine examination in the trial, except that CT/MRI scan obtained before signing informed consent may be used for screening evaluation if they meet the criteria. The examination must be performed within the first 28 days of the date of the randomization.).

(11) Echocardiography: especially analysis of the values of LVEF (assessments before signing informed consent or within 28 days before randomization if necessary).

(12) Epidemiology: HBs-Ag, Anti-HCV, syphilis, and HIV. HBV DNA test is required if HBs-Ag positive, and HCV RNA test for anti-HCV antibody-positive patients.

(13) Concomitant medications and therapy: assessments of concomitant medication and concomitant therapy within 28 days before enrollment and during the trial period.

(14) Documentation of AEs: Record AEs from the first dose of the study drug.

The following screening procedures must be completed within 7 days before initiating drug therapy (Blood tests including hemanalysis, blood biochemistry, and coagulation function within 2 weeks before randomization is performed.):

(1) ECOG PS;

(2) Vital signs: Heart rate, respiratory rate, temperature, and BP;

(3) BP monitoring;

(4) Physical examination: Facial features, integumentary system, lymph nodes, eyes, ears, nose, throat, oral, respiratory system, cardiovascular system, abdomen, urinary tract system, musculoskeletal system, nervous system, and spiritual state;

(5) Hemanalysis: Hemoglobin, red blood cell, white blood cells, absolute neutrophil count, lymphocyte count, and platelet count;

(6) Urinalysis: Urine protein, glucose, occult blood (red blood cell and white blood cell), pH, and ketone bodies; If the semi-quantitative method shows the levels of protein ≥2+ (e.g., urine test strip), 24-hour urine analysis are performed and the 24-hour urine analysis of enrolled patients must be < 1g;

(7) Stool tests: occult blood;

(8) Blood biochemistry: TBil, ALT, AST, ALP, r-GT, total protein, Cr, UA, blood glucose, triglyceride, cholesterol, potassium, sodium, chlorine, calcium, urea, and phosphonium;

(9) Coagulation tests: PT, APTT, TT, Fbg, and INR;

(10) ECG: 12-lead ECG. A prolongation of PR-, QTc-, and QT-intervals should be observed and ECG can be performed 3 times consecutively to identify abnormalities (approximately 5-minute interval for each examination and a prolongation of QTc- should be indicated);

(11) Myocardial enzyme profile test: No more myocardial enzyme profile tests except for one test performed within 7 days before enrollment (testing is required if the ECG is abnormal).

(12) Pregnancy test (women of childbearing age);

(13) QoL: The questionnaire should be completed by the subject himself/herself. However, if the subject is unable to read or write, an authorized staff member or guardian could administer it.

The following screening procedures must be performed in screened patients.

1. Subjects who meet eligibility criteria will be randomized by a web-based system and assigned a subject number and treatment groups as well as obtain the dose of the study drug.
2. Study drug administration.
   1. **Treatment period**

Subjects who meet the criteria are administered the treatment in cycles of 21 days. The visits are conducted on days 21±3 of each cycle for the first 4 cycles, on days 42±3 per 2 cycles for the following 22 cycles, and on days 63±7 per 3 cycles from 27 cycles until the disease progresses or intolerable toxicity.

1. Vital signs: Heart rate, respiratory rate, temperature, and blood pressure;
2. Physical examination: Facial features, integumentary system, lymph nodes, eyes, ears, nose, throat, oral, respiratory system, cardiovascular system, abdomen, urinary tract system, musculoskeletal system, nervous system, and spiritual state;
3. BP monitoring: BP is measured by the subject himself/herself and recorded in the patient diary card. BP is tested at least 3 times per week for the first 2 cycles and followed up each day if the blood pressure was abnormal. In addition, BP is measured again by the investigator at each follow-up visit, coffee and tobacco intake are prohibited within 30 minutes before each BP is measured and the measurement is taken in the sitting position with the arm at heart level after at least 10 minutes of quiet sitting, and each BP measurement is taken on the same side;
4. Hemanalysis: Hemoglobin, red blood cell, white blood cells, absolute neutrophil count, lymphocyte count, and platelet count;
5. Urinalysis: Urine protein, glucose, occult blood (red blood cell and white blood cell), pH, and ketone bodies; If the semi-quantitative method shows the levels of protein ≥2+ (e.g., urine test strip), 24-hour urine analysis is performed;
6. Blood biochemistry: TBil, ALT, AST, ALP, r-GT, total protein, Cr, uric acid (UA), blood glucose, triglyceride, cholesterol, potassium, sodium, chlorine, calcium, urea, and phosphonium;
7. 12-lead ECG. A prolongation of PR-, QTc-, and QT-intervals should be observed. If symptoms such as precordial pain and palpitations occur, an ECG should be checked immediately, together with an additional cardiac enzyme profile; LVEF is required for ECG abnormalities with significant clinical significance.
8. Stool tests: Occult blood;
9. Coagulation tests: PT, APTT, TT, Fbg, and INR;
10. Imaging examination (cycle 1 days 21±7 and days 21±7 per 3 cycles from 27 cycles):

- The window duration of the image is not impacted by drug interruption and is performed according to the baseline;
- The target lesion identified at baseline should be examined under the same conditions as the baseline examination (layer thickness of the scan, use of contrast agent, etc.); Patients with bone metastases detected at baseline should be examined again and other lesions other than the above or new lesions suspected should also be detected.
- Unscheduled imaging may be performed when disease progression is suspected (e.g., worsening of symptoms) or when confirmation of PR or CR is required (6 weeks after achieved PR or CR);

1. QoL: Conducting by the investigator asking questions and the subject answering;
2. ECOG PS;
3. AEs: Recording AEs from the date of the first dose of the study drug to at least 30 days after the last dose and follow up until the AEs resolved or stabilized;
4. Concomitant medications: Concomitant medications and therapy during the trial should be recorded and if the subject discontinues treatment, the concomitant medication and therapy are recorded only in the case of a novel or unresolved AEs associated with treatment;
5. Study drug: Distribution and recovery of study drug.
   1. **End-of-treatment and withdrawal study**

At the end-of-treatment and withdrawal study, if the patient is not examined within 14 days before the end of treatment, the following tests should be performed.

1. ECOG PS;
2. Vital signs: Heart rate, respiratory rate, temperature, and BP;
3. Physical examination: Facial features, integumentary system, lymph nodes, eyes, ears, nose, throat, oral, respiratory system, cardiovascular system, abdomen, urinary tract system, musculoskeletal system, nervous system, and spiritual state;
4. BP monitoring: BP is measured by the investigator, coffee and tobacco intake are prohibited within 30 minutes before each BP is measured and the measurement is taken in the sitting position with the arm at heart level after at least 10 minutes of quiet sitting, and each BP measurement is taken on the same side;
5. Hemanalysis: Hemoglobin, red blood cell, white blood cells, absolute neutrophil count, lymphocyte count, and platelet count;
6. Urinalysis: Urine protein, glucose, occult blood (red blood cell and white blood cell), pH, and ketone bodies; If the semi-quantitative method shows the levels of protein ≥ 2+ (e.g., urine test strip), 24-hour urine analysis is performed;
7. Blood biochemistry: TBil, ALT, AST, ALP, r-GT, total protein, albumin, Cr, uric acid (UA), blood glucose, triglyceride, cholesterol, potassium, sodium, chlorine, calcium, urea, and phosphonium;
8. Stool tests: Occult blood;
9. Coagulation tests: PT, APTT, TT, Fbg, and INR;
10. 12-lead ECG;
11. Pregnancy test;
12. QoL;
13. AEs;
14. Recovery drug;
15. Imaging examination: If imaging is not performed within 4 weeks before the end of treatment, an imaging examination is required at the end of study treatment or withdrawal study. For patients with non-imaging progression (intolerable, other conditions), tumor evaluation performs every 2 cycles until disease progression, death, or the initiation of other oncologic therapy.
    1. **30-day post-withdrawal follow-up**

Safety assessment and follow-up of AEs should be continued for all subjects 30 days after the end of the last dose, with documentation of concomitant therapy.

1. Documentation of concomitant medications and therapy;
2. Follow-up of AEs.
   1. **Follow-up of survival**

Subjects who end the 30-day visit after drug discontinuation will start the follow-up of survival. Information of survival (record the date and cause of death) and end-of-treatment (including treatment) period is collected by telephone (asking the subjects and their relatives or a local physician) at least once every 3 months until death or subjects loss of visit or termination of the study by the sponsor. Each follow-up of survival is recorded in the follow-up format.

- 1. **Unplanned follow-up**

Subjects may experience AE requiring unplanned follow-up during the trial as follows.

1. Documentation of concomitant medications and therapy;
2. Follow-up of AEs
3. Documentation of relevant examinations (if have).
4. Study Assessments
   1. **Efficacy assessment**
      1. **Primary endpoint**

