7. Pregnant or lactating women; A fertile patient who is unwilling or unable to use effective contraception;
8. The investigator identifies other conditions that may affect the proceeding of the clinical study and its outcomes.
   1. **Dropout/removal criteria**
9. Patients who failed to meet the inclusion criteria;
10. Safety evaluation could not be performed without one dose of the drug;
11. Both modern Chinese medicine and immunomodulators approved by SFDA are simultaneously used for the treatment of lung cancer;
12. The dose, method, and course of treatment are not specified according to the study protocol.
    1. **Termination criterion**
13. Withdrawl of informed consent and request to withdraw from the study;
14. Radiographic evidence of disease progression;
15. Pregnancy events occurred during the study;
16. Subjects who were still unable to tolerate toxicity after dose adjustment;
17. Decisions to withdraw from study by the sponsor.
18. Study Drugs
    1. **Overview of drugs**
       1. **Drug information**

Study Drugs are produced by Chia Tai Tianqing Pharmaceutical Group Co., Ltd., and the detailed information is shown in Table 6.1.1.

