**Table 6.1.1 Drug Information**

| **Drugs** | **Specification** | **Drug storage** | **Manufacturer** |
| --- | --- | --- | --- |
| Anlotinib | 12 mg/tablet  10 mg/tablet  8 mg/tablet | Store in a sealed and dark place below 25°C | Chia Tai Tianqing Pharmaceutical Group Co., Ltd. |
| Placebo | 0 mg/tablet | Store in a sealed and dark place below 25°C | Chia Tai Tianqing Pharmaceutical Group Co., Ltd. |
| Gefitinib | 250 mg/tablet | Store at a room temperature of 15-30°C | Chia Tai Tianqing Pharmaceutical Group Co., Ltd.  Astrazeneca Pharmaceuticals Co., Ltd. |

Anlotinib and placebo are produced by Chia Tai Tianqing Pharmaceutical Group Co., Ltd., and batch numbers and expiration dates are detailed in the drug test report. Gefitinib tablets are produced by Chia Tai Tianqing Pharmaceutical Group Co., Ltd. or purchased from Astrazeneca Pharmaceuticals Co., Ltd.

- - 1. **Drug packaging**

Anlotinib is packaged in capsules, with 7 tablets per plate and 2 plates per small box.

- 1. **Dose and administration regimens**

Group A (experimental group): 250 mg gefitinib, po, qd + 12 mg anlotinib hydrochloride capsule, po, qd, D1-D14; administered under fasting conditions (taking medication at the same time every day), every 3 weeks;

Group B (control group): 250 mg gefitinib, po, qd + anlotinib hydrochloride mock capsule, 1 tablet, po, qd, D1-D14; administered under fasting conditions (taking medication at the same time every day), every 3 weeks.

Anlotinib is given at a dose of 12 mg as the initial dose (po, qd, D1-D14) every 21 days and the drug combination is used until disease progression, intolerable toxicity, withdrawal of consent, or drug discontinuation according to the investigator's judgment. If the administration is suspended due to no recovery of drug toxicity, treatment cycle is recalculated according to the regimen of consecutive 2 weeks and stop 1 week, while the follow-up period is still calculated according to the screening date. If patients discontinue anlotinib due to intolerable toxicity, gefitinib can be continued until disease progression.

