The investigator may destroy the used study drugs (non-state controlled chemicals) and empty boxes/bottles after written notification to the co-organizer without endangering the health of the population. The investigator should keep all study drug-handling records.

These records must document the evidence and quantity of each batch of destroyed drugs, disposal methods (as required by local law), and the person who handled the study drugs.

1. Dose Adjustment and Discontinuation
   1. **Dose adjustment of anlotinib**

The initial dose of anlotinib or placebo is 12 mg/day, and the anlotinib dose can be reduced to 10 mg/day for the first dose and 8 mg/day for the second dose. For patients unable to tolerate a dose of 8 mg/day, anlotinib should be discontinued and gefitinib should be administered alone until PD or intolerable toxicity.

|  | **Study group (anlotinib)** | **Control group (placebo)** |
| --- | --- | --- |
| Initial dose | ■■ 12 mg/day, qd | □□ 12 mg/day, qd |
| First dose reduction | ● 10 mg/day, qd | ○ 10 mg/day, qd |
| Second dose reduction | ■ 8 mg/day, qd | □ 8mg/day, qd |
| Third dose reduction | Discontinuation | Discontinuation |

- 1. **Dosage suspension and reduction**

If dosage suspension caused by drug toxicity has not recovered, the duration of dosage suspension should not exceed 6 weeks per cycle. Follow-up visits will be conducted at least every 1-2 weeks during discontinuation and the drug will be restarted at the original dose or a lower dose level after recovery of toxicity.

The subjects cannot return to the previous dosing pattern after dosage reduction and a maximum of three dose reductions are allowed in anlotinib therapy.

When patients experienced grade 3 hematological toxicities and grade 2 non-hematological toxicities, dosage suspension and reduction are considered; Dosage suspension will be performed in non-hematological toxicities including controllable nausea, vomiting, and fever with a definite cause (below 38°C) until the toxicity became tolerable. Aggressive symptomatic management without dosage suspension and reduction can also be conducted.

- - 1. **Standardization of dose suspension and reduction**

To ensure consistency of dosage adjustment, dosage suspension is performed at the time of dosage adjustments for each cycle. The criteria of dose suspension and reduction are as follows (once the criteria of dosage reduction are met which is considered poorly tolerated, a reduction should be performed).

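### Section 7.4 withdraws patients from the study for four anlotinib-related toxicities, against 7.2 and 9.3, so PFS assessments can be lost unequally between the arms

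*Protocol*

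**What the plan says.** **Orders to leave the study (7.4).**
- Any arterial thrombosis: "drug administration should be discontinued immediately and the study should be withdrawn".
- Venous thrombosis: "If symptomatic grade IV venous thrombosis occurs, drug administration should be discontinued in patients, with withdrawal from the study".
- RPLS: "Once confirmed by imaging, patients are withdrawn from the clinical trial".
- Perforation, under Abdominal pain: "Once gastrointestinal perforation occurs, the administration should be discontinued immediately, withdrawal from the trial, with symptomatic treatment".

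**Overlapping events in the 7.2 dose adjustment table.** The row on events of special interest names arterial thrombosis, grade IV venous thrombosis, leukoencephalopathy syndrome and gastrointestinal perforation. It recommends interrupting the drug and treating symptoms. It does not mention leaving the study.

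**General intolerance.** Section 5.5, headed only as a termination criterion, lists "Subjects who were still unable to tolerate toxicity after dose adjustment". The same list contains withdrawal of consent, a sponsor decision to withdraw the patient from the study, and radiographic progression. Section 7.1 says of patients who cannot tolerate 8 mg/day that "anlotinib should be discontinued and gefitinib should be administered alone until PD or intolerable toxicity". Section 6.2 allows the same: "If patients discontinue anlotinib due to intolerable toxicity, gefitinib can be continued until disease progression".

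**Follow-up.** For patients who stop without radiological progression, 9.3 says "tumor evaluation performs every 2 cycles until disease progression, death, or the initiation of other oncologic therapy". Section 9.5 starts survival follow-up after the 30-day visit that follows drug discontinuation. For PFS, 10.1 censors patients who discontinue for a reason other than progression, and have no later tumour image, at discontinuation.

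**The concern.** The protocol does not separate stopping a study drug from leaving follow-up. For the four events in 7.4, a site has one instruction that ends participation, one that only interrupts the drug (7.2), and one that keeps the patient under tumour evaluation (9.3). Which one it follows decides whether later scans exist.

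That matters for the primary endpoint. Without later scans, 10.1 censors the patient at discontinuation. Section 7.4 covers anlotinib-related events, so such censoring would plausibly be more frequent in the experimental arm. It would also come just as the patient loses the added drug. If the hazard of progression rises at that point, the censoring is informative and favours anlotinib. Scans that were never made cannot be recovered at analysis.

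**Working it through.** **1. The passages side by side**

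| Situation | Ends participation? | Keeps the patient in? |
|---|---|---|
| Arterial thrombosis, grade IV venous thrombosis (7.4: symptomatic), RPLS or leukoencephalopathy, perforation | 7.4: yes, explicitly | 7.2: drug interruption only; 9.3: scans continue after a non-progression stop |
| Intolerance after dose reduction | 5.5: not stated | 7.1 and 6.2: gefitinib continues or may continue; 9.3: scans continue |

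The first row is a direct conflict. The second is an ambiguity.

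**2. The plan's own design figures (3.3)**

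Inputs: medians of 15 and 10 months, two-sided α of 0.05, power of 80%, 18 months' accrual plus 18 months' follow-up, 20% dropout.

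- HR under exponential PFS: 10/15 = 0.667.
- Events (Schoenfeld): 4 × (1.960 + 0.842)² / (ln 0.667)² = 191, against 192 stated. With 192 events the power is 80.2%.
- Event probability: 1 − (e^(−18λ) − e^(−36λ)) / (18λ), with λ = ln 2 / median. This gives 0.704 (experimental) and 0.836 (control).
- With 124 per arm: 87.4 + 103.7 = 191.0 events. Stated: 88 + 104 = 192.
- Enrolment: 248 / 0.8 = 310.

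These figures reproduce and are not in dispute. With all 310 patients followed, 155 × (0.704 + 0.836) ≈ 239 events are expected.

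**3. What censoring at withdrawal would do**

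The protocol gives no rate for the 7.4 withdrawals and no hazard after stopping. Both are assumptions here.

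*Scenario A.* Simulated exponential PFS with the inputs of step 2. Withdrawal times are uniform over months 0–8. The hazard after stopping is 1, 1.5 or 2 times the control hazard (ln 2 / 10). Each cell compares the Cox HR with full follow-up against the HR with censoring at withdrawal. Shifts are rounded to 0.005 because of simulation error.

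| Withdrawn, anlotinib / control | HR, full follow-up | HR, censored | Shift | PFS events lost per 310 |
|---|---|---|---|---|
| 2% / 0% | 0.67–0.68 | about 0.67 | 0.005–0.01 | 2–3 |
| 5% / 1% | 0.68–0.69 | about 0.67 | 0.01–0.025 | 6–7 |
| 10% / 2% | 0.69–0.71 | about 0.67 | 0.02–0.045 | 12–14 |

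In the 10% / 2% case about 228 events are still observed among 310 patients, above 192.

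*Scenario B.* The same withdrawal rates, with times uniform over months 0–6 and the hazard after stopping a multiple of the patient's own arm's hazard.
- Hazard unchanged: the HR does not shift.
- Hazard doubled (ratio of exponential rates): 0.674 with full follow-up against 0.666 censored, 0.682 against 0.667, and 0.699 against 0.668. The shift is about 0.01 to 0.03.
- Events lost per 155 per arm, hazard unchanged: 1.8 / 0, 4.5 / 1.0 and 8.9 / 2.0 (anlotinib / control).
- Power with 124 per arm at a fixed calendar cut-off, hazard unchanged: from 80.0% to 79.7%, 79.1% and 78.1%.

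**The case against.** The strongest reply is that the protocol already provides the follow-up and uses the word withdrawal loosely. The heading of 9.3 covers both end of treatment and withdrawal, and 9.3 asks for imaging at either. Section 9.4 calls its visit post-withdrawal but times it from the last dose. Section 9.5 then follows survival until death, loss to follow-up or termination by the sponsor. A careful site could read 7.4 in that light and lose nothing. This stands as a reason why the damage may be small. It does not remove the conflict, because 7.4 speaks of leaving the study or trial as well as of stopping the drug, and 7.2 treats overlapping events differently.

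The events may also be rare. Section 7.4 says RPLS has not been reported in completed anlotinib trials and perforation only occasionally. The 12 mg adverse event table (21 patients) lists no thrombosis, RPLS or perforation. That supports the lower end of the assumed rates.

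Several stronger readings are tempting, but the documents do not support them:
- *That 5.5 removes every intolerant patient from the study.* It also lists radiographic progression. If meeting it ended follow-up, survival data would be lost for every progressing patient, contrary to 9.5. It can be read as stopping treatment.
- *That 6.2 and 7.1 keep a patient with arterial thrombosis on gefitinib.* They address general intolerance of anlotinib, not the four events in 7.4.
- *That the HR would describe only patients who tolerated anlotinib.* Censored patients contribute time and events until withdrawal.
- *That the event target is in danger.* Withdrawing 10% and 2% is 6% of all patients, inside the 20% dropout allowance, and the final analysis is triggered by about 192 events.

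**Conclusion.** The conflict between 7.4 and both 7.2 and 9.3 is real, and 5.5 is ambiguous beside 7.1. Through the censoring rule in 10.1, a literal reading of 7.4 can bias PFS, plausibly towards anlotinib.

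The likely size is modest: an HR shift of about 0.005 to 0.045 and about 2 to 14 lost events per 310 patients. This rests on assumed withdrawal of 2–10% against 0–2%, on sites actually ending imaging, and on a hazard after stopping of one to two times the control hazard. If the hazard does not change when the drug stops, the HR does not shift. Rates of 15–20% would need the contested reading of 5.5 and are not used here.

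A reader might infer that OS is lost in the same way. That is weaker: 9.5 already starts survival follow-up after drug discontinuation, although it does not say that patients withdrawn under 7.4 are included.

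This should be fixed, but it does not invalidate the design.

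**What to change.** - State in 5.5 and 7.4 that withdrawal because of toxicity does not end follow-up.
- State that every randomised patient continues tumour evaluation under 9.3 (to progression, death or new anticancer therapy) and survival follow-up under 9.5, unless consent to follow-up is withdrawn or the patient is lost or dies.
- Ask the sponsor to reconcile 5.5, 6.2, 7.1, 7.2 and 7.4 on whether each drug is interrupted, stopped or continued for these events. No clinical rule is proposed here.

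The cost is amendment wording, since the scans and telephone contacts already stand in 9.3 and 9.5. The downside is continued follow-up of a few patients whom some sites would otherwise release.
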